### Adverse events

All unexpected responses related to acupuncture treatment or use of artificial tear drops will either be reported to the investigators by participants or be examined by acupuncture practitioners. Local, general and psychological adverse events are possible as a result of acupuncture treatments [13]. Irritability, pain and redness of eyes, headache, and blurred vision are recognised as common adverse reactions to artificial tear drops. If serious adverse events (SAE) occur, experimental treatments will be stopped immediately, and appropriate treatments will be offered. The type and frequency of adverse events will be reported for each group.

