### Intervention

#### Acupuncture treatment

Certified acupuncture practitioners who have a minimum of 7 years of training and 3 years of clinical experience will perform the acupuncture treatments. They will take a one-day training course for this trial. This course will cover the study protocol, techniques for acupuncture treatment, the recording method for the clinical record form (CRF), and basic information about clinical research, a researcher's duty and research monitoring. The relationship between patients and practitioners can be an important factor when assessing the outcomes of acupuncture research [15]. Therefore, interactions between acupuncture practitioners and participants will be strictly limited, except when reporting adverse events.

Based on a literature review and a textbook about acupuncture for ophthalmologic diseases or dry eye [16], acupuncture points were chosen by an expert committee comprised of professors and researchers that specialise in acupuncture and ophthalmology of traditional Korean medicine. Seventeen acupuncture points (bilateral BL2, GB14, TE 23, Ex1, ST1, GB20, LI4, and LI11 and single GV23) will be located according to the WHO Standard Acupuncture Point Locations in the Western Pacific Region [17]. These will then be treated with 0.20*30 mm disposable acupuncture needles (Dongbang Co., Korea). The '*deqi*' sensation will be induced by twisting acupuncture and needles will be retained for 20 minutes before removal. Participants will have acupuncture treatments three times per week for four weeks.

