#### Active comparator group using artificial tear drops

Artificial tear is one of the first choices in treatment for dry eye. Because the strategy for treating dry eye is to ease ocular discomfort and to improve quality of life, and to recover the ocular surface from chronic inflammation and tear film instability [18], artificial tear can be recommended as an active treatment. According to a survey report of ophthalmologists, preservative-free artificial tear was the most frequently selected medication for moderate to severe dry eye patients among various treatment modalities in Korea [19]. In this context, we chose preservative-free artificial tear as an active comparator intervention in this trial.

Participants allocated to this group will be offered preservative-free and one-day-use artificial tear drops (Refresh Plus^®^, ALLERGAN) and then educated on how to use them. According to the participants' discomfort from dry eye symptoms, it is recommended that the tear drops can be used at least once a day for four weeks. A diary of both the frequency and quantity of drops used will be collected at every visit.

In both groups, other treatments for dry eye will be forbidden during the study period. These other treatments include different types of artificial tear drops, drugs, supplements (e.g. cyclosporine, corticosteroids, biological tear substitute, and oestrogen), and alternative treatments (e.g. herbal medicine, acupuncture, and cupping therapy). However, participants will be allowed to use any kind of treatment for dry eye during the follow-up period. The usage of these treatments will be reported during the follow-up period.

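### As written, the adverse-event rule covers only unexpected, treatment-related responses and collects them unevenly, so the by-group frequencies may be incomplete and biased

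*Protocol article*

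**What the plan says.** The capture rule is in the Adverse events section: "All unexpected responses related to acupuncture treatment or use of artificial tear drops will either be reported to the investigators by participants". The alternative route follows in the same sentence: "or be examined by acupuncture practitioners". The rule thus carries two qualifiers, *unexpected* and *related*, and gives two routes: participant report and examination by acupuncture practitioners.

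The section then describes what is foreseen. For acupuncture: "Local, general and psychological adverse events are possible as a result of acupuncture treatments". For the comparator: "Irritability, pain and redness of eyes, headache, and blurred vision are recognised as common adverse reactions to artificial tear drops". It ends with the planned output: "The type and frequency of adverse events will be reported for each group". That sentence has neither qualifier.

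On contact, the Acupuncture treatment section says: "Participants will have acupuncture treatments three times per week for four weeks". It also says that "interactions between acupuncture practitioners and participants will be strictly limited, except when reporting adverse events". The comparator is self-administered. For that arm the article says: "A diary of both the frequency and quantity of drops used will be collected at every visit". The diary as described covers drop use, and the number of visits is not given. The OSDI is assessed in both arms at weeks 1, 3, 5, 9 and 13. Under Randomisation and Allocation Concealment, the envelope is opened in front of the participant, so allocation is known to the participant.

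**The concern.** There are two separate problems.

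**Scope.** A reaction that the protocol itself calls common is, in the ordinary sense, expected. If staff follow the sentence literally, such reactions fall outside the rule, and so do events that nobody attributes to treatment. The *related* qualifier is awkward in this disease. Eye pain, redness and blurred vision are listed as reactions to tear drops, and they also appear among the dry eye symptoms in the eligibility criteria or the VAS items. Whether such a complaint counts depends on an attribution, in a trial where participants know their treatment.

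**Ascertainment.** The examination route names only acupuncture practitioners, and one arm sees them repeatedly. Events may be found more often in that arm simply because there are more occasions to find them.

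The Background says that the safety of acupuncture is not well established, so the per-group safety table will be read with interest. No later analysis can recover events that were never recorded.

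**Working it through.** The plan states no figure on this point, so there is none to reproduce. The check is a comparison of passages, a count of contacts, and an illustration on assumed values.

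**1. Rule against output (Adverse events section).**

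| Type of event | Covered by the rule, read literally? | Covered by the promised report? |
|---|---|---|
| Unexpected and related | Yes | Yes |
| Recognised reaction to the assigned treatment | No (expected) | Yes |
| Untoward event not attributed to treatment | No (not related) | Yes |

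Two of the three rows do not match.

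**2. Contacts.** Acupuncture: 3 sessions per week × 4 weeks = 12. Assessments common to both arms around treatment: weeks 1, 3 and 5, so at most 3, or 2 after treatment starts. The ratio is 12/3 = 4 to 12/2 = 6, if the tear arm has no other visits. That condition is an assumption.

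**3. Illustration of unequal detection.** Assume that the same persisting complaint exists in both arms, that contacts are independent, and that each contact brings it to light with probability q. Ignore spontaneous reports. The chance of detection over k contacts is 1 − (1 − q)^k.

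| q (assumed) | k = 12 | k = 3 | k = 2 | Ratio 12 v 3 | Ratio 12 v 2 |
|---|---|---|---|---|---|
| 0.05 | 46% | 14% | 10% | 3.22 | 4.71 |
| 0.10 | 72% | 27% | 19% | 2.65 | 3.78 |
| 0.20 | 93% | 49% | 36% | 1.91 | 2.59 |
| 0.30 | 99% | 66% | 51% | 1.50 | 1.93 |
| 0.50 | 100% | 88% | 75% | 1.14 | 1.33 |

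For example, at q = 0.10: 1 − 0.9^12 = 0.718 and 1 − 0.9^2 = 0.190, ratio 3.78.

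Adding the week 9 and 13 visits to both arms gives 14 against 4 contacts. At q = 0.10: 1 − 0.9^14 = 0.771 and 1 − 0.9^4 = 0.344, ratio 2.24. At q = 0.50: 1.00 and 0.94, ratio 1.07.

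**4. In numbers of reports.** Take the planned 75 per arm and assume a true risk of 20% in both arms. With 90% detection in the acupuncture arm: 75 × 0.20 × 0.90 = 13.5 reports. In the tear arm, 60% detection gives 75 × 0.20 × 0.60 = 9.0 (ratio 1.5), and 40% gives 6.0 (ratio 2.25). Equal detection would give 13.5 in each.

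The contact effect inflates the acupuncture arm relative to the tear arm at every value tried. Its size depends entirely on the assumed detection chances.

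**The case against.** The strongest reply is that this is one loose sentence in a condensed article. *Unexpected* may simply mean untoward. The section calls the foreseen reactions adverse events or adverse reactions, its final sentence is unqualified, and the Acupuncture treatment section speaks of reporting adverse events without a filter. Nothing says that other events will not be recorded. This stands as far as intent goes: wider recording may well be meant. It does not rescue the wording, because the only capture rule given still carries both qualifiers, and under the looser reading the *related* filter and the uneven routes remain.

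A reader might infer more than the documents support:

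- *That the frequencies will certainly be incomplete and not comparable.* Participants in both arms can report to the investigators, and the amount of any bias cannot be derived from the article.
- *That causality is judged before recording by people who know the allocation.* Knowledge of allocation is documented for participants, but no passage says who judges relatedness or when.
- *That tear participants have no scheduled reason to meet a practitioner.* The week 5 general assessment by acupuncture practitioners is not restricted to one arm and may bring them to one.
- *That the tear arm has only two contacts.* The number of visits is not stated, and the flow chart is not available here.

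It is also fair to say that more sessions are inherent in comparing a clinic-delivered treatment with a self-administered one, that the safety output is descriptive, and that the primary aim concerns the OSDI. Unequal treatment contact is indeed unavoidable. Unequal eliciting of events is not, because common visits already exist. Finally, the layout of the record form is properly left to the full protocol. The point here rests on what the article states, not on that missing detail.

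**Conclusion.** The point holds in a limited form. As written, the capture rule is narrower than the report it must feed, and it provides an examination route that favours detection in one arm. The per-group frequencies may therefore be incomplete in both arms and tilted between them.

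The contact imbalance pushes towards more recorded events with acupuncture. The *unexpected* and *related* filters can remove events from either arm, so the net direction is not certain. The documents do not fix the size. The apparent ratios of 1.1 to 4.7 under equal true risk, with 12 contacts against 2 or 3, rest on assumed detection chances, a persisting complaint, independent contacts and no further control visits. They show that the effect could range from minor to substantial, and they are not an estimate.

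The primary comparison is not affected. This is a cheap improvement, but it has to be made before data collection.

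**What to change.** - Replace the capture sentence so that any untoward event after allocation is recorded, whatever its expectedness or suspected relation to treatment.
- Elicit events with the same standard question in both arms at the existing common visits (weeks 3, 5, 9 and 13), asked by the outcome assessors whom the trial already has for the self-reported outcomes.
- Record relatedness and expectedness afterwards, as attributes of each event and not as conditions for entry.
- Base the between-group table on the common-visit elicitation. List events noted at acupuncture sessions separately, so that they are not lost and do not enter the comparison. Show weeks 3 and 5 apart from weeks 9 and 13, because other dry eye treatments are allowed during follow-up.

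The cost is a change of wording and one question on the record form at visits that already take place, with no new visits or staff. The downside is more events to code, most of them minor.

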### Ethics

This research protocol was approved by the institutional review board (IRB) of each trial centre (Daejeon University Hospital, Dongguk University Ilsan Oriental Hospital and Dongshin University Gwangju Oriental Hospital). Every participant will give informed consent before the start of this trial.

## List of abbreviations

ANCOVA: analysis of covariance; CRA: clinical research associate; CRF: clinical record form; IRB: the institutional review board; LOCF: last observation carried forward; MYMOP-2: Measure Yourself Medical Outcome Profile-2; OSDI: ocular surface disease index; TFBUT: tear film break-up time; VAS: visual analogue scale; QOL: quality of life
